To quantify tendon structure, contours will be manually placed around the Achilles tendon in the transverse view at regular intervals along the length of the Achilles tendon (disappearance of the calcaneus to the musculotendinous junction) [44]. The UTC software (UTC2010, UTC Imaging) automatically interpolates between the contours to create a 3-D volume where proportions of each echo type are calculated. The percentage of echo type I + II (structure-related) and echo type III and IV (non-structure related) will be then be calculated. The percentage of normal tendon (i.e. echo types I and II) will then be determined from this data [57].(ii)Participant perception of the treatment effect: the participant’s perception of treatment effect will be measured separately for pain and function using the Patient Global Impression of Change (PGIC) questionnaire [58]. The scale includes the following questions for participants: ‘Compared to how you were before starting this trial, how is your pain in your Achilles tendon?’, and ‘Compared to how you were before starting this trial, how would you rate your ability to perform physical activities (such as walking, dancing, running, gardening, housework)?’. Each question will have the following responses ‘very much improved’, ‘much improved’, ‘minimally improved’, ‘no change’, ‘minimally worse’, ‘much worse’, or ‘very much worse’. The responses will then be dichotomised according to ‘treatment effectiveness’ where ‘treatment effectiveness’ is defined as ‘much improved’ or ‘very much improved’ [59].(iii)The severity of pain: the severity (intensity) of pain will be measured using a 100 mm VAS, where participants will be asked to, ‘Mark on the line the severity of pain you have experienced in your Achilles tendon when it has been at its worst, over the past week’. Zero (0) implies no pain and one hundred (100) implies the worst pain imaginable [58].(iv)Health status: EuroQol (EuroQol 5D-5 L®), a standardised questionnaire for describing health-related quality of life, will be used to measure health status [60]. This measurement tool consists of five questions addressing mobility, self-care, usual activities, pain/discomfort, and anxiety/depression. The participant will also rate their overall health state from 0 (worst health state imaginable) to 100 (best imaginable health state) using a VAS.(v)Level of physical activity in the previous week: the level of physical activity in the previous week will be evaluated using the 7-day Recall Physical Activity Questionnaire, a valid and reliable tool [61]. This questionnaire has been used previously as an outcome measure in clinical trials of interventions for lower limb musculoskeletal pathologies including Achilles tendinopathy [25, 59].(vi)Calf muscle function: calf muscle function will be measured at baseline and at 12 weeks using the standing heel rise test [62]. This test involves participants using their fingertips lightly placed on a wall for balance, whilst minimising postural sway, standing on their affected side and then repetitively raising onto their toes (moving the ankle into plantarflexion) until fatigue. This test will be performed to the sound of a metronome (one heel rise every 2 s with a metronome set at 60 beats per minute). The maximum number is then recorded. This test has been previously used and shown to have adequate reliability (ICC = 0.61 to 0.98) in both healthy participants [63] and participants with Achilles tendinopathy [64, 65]

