### Statistical analysis

The most recent version of SPSS (IBM Corp., Armonk, NY, USA) will be used to perform statistical analysis. The intention-to-treat principle will be used for all randomised participants. Where participants have bilateral symptoms, the more painful side will be analysed (or the right side if they cannot define the more painful side) to maintain independence of data. Multiple imputation will be used to replace any missing data using five iterations, with sex, age, baseline scores, and group allocation as predictors [67]. However, data substitution will not be applied for the following variables; self-reported magnitude of symptom change, use of co-interventions, adherence and adverse events. Standard tests to assess continuous data for normal distribution (such as assessing skewness and kurtosis) will be used and transformation carried out if required.

The primary outcome measure will be the VISA–A questionnaire measured at 12 weeks. To avoid over-testing and to minimise the risk of type I error associated with serial measurements, statistical analysis of the efficacy of the interventions will specifically focus on the change in primary outcome measures between baseline and 12 weeks [70, 71], and differences in the primary and secondary outcome measures between the two groups will be compared at 12 weeks. To minimise regression to the mean, continuously-scored outcome measures will be analysed using analysis of covariance (ANCOVA) with baseline scores, and intervention group entered as independent variables [72]. Relative risk, risk difference, and number needed to treat (NNT) will be used to compare dichotomous-scaled outcome measures. To complement point estimates, 95% confidence intervals and *p*-values will be calculated where appropriate.

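### The PGIC is exempt from imputation, so its week-12 RR, RD and NNT use responders to the questionnaire only, while other efficacy outcomes are imputed for all randomised participants

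*Protocol article*

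**What the plan says.** The Statistical analysis section of the protocol article sets the population rule: "The intention-to-treat principle will be used for all randomised participants". The general missing-data rule follows: "Multiple imputation will be used to replace any missing data using five iterations, with sex, age, baseline scores, and group allocation as predictors". An exception comes next: "data substitution will not be applied for the following variables; self-reported magnitude of symptom change, use of co-interventions, adherence and adverse events".

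Under Secondary outcome measures, the "participant’s perception of treatment effect will be measured separately for pain and function using the Patient Global Impression of Change (PGIC) questionnaire". Each item has seven response categories, and the top two count as treatment effectiveness. No other outcome in the list is given a success cut-off.

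For the comparison, the Statistical analysis section says that "Relative risk, risk difference, and number needed to treat (NNT) will be used to compare dichotomous-scaled outcome measures", and that "differences in the primary and secondary outcome measures between the two groups will be compared at 12 weeks".

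The exception does not use the name PGIC. It is, however, the only listed outcome that asks participants to rate their change since before the trial, and the Discussion describes it as a global rating of change. No other outcome fits.

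**The concern.** Three of the four exempt variables (co-interventions, adherence, adverse events) are not efficacy outcomes, and leaving them unimputed is reasonable. The fourth is an efficacy outcome, and the protocol gives no reason for placing it with the others. No other rule for a missing PGIC response appears. A bar on substitution, read naturally, also excludes counting a missing response as not effective. What remains is an available-case analysis.

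A participant with no week-12 data would then count towards the VISA-A and pain VAS comparisons but not the PGIC comparison, so results reported side by side would describe different sets of people. The NNT, which clinicians are likely to quote, would come entirely from the exempt measure. If the chance of a missing response depends on how the participant fared, and does so to a different extent in the two arms, the risk difference and NNT are biased. Differential loss is plausible on the protocol's own account: it describes the exercise programme as time-consuming and demanding with variable adherence, and participants are not blinded.

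**Working it through.** **The plan's own figure.** The only relevant number is the sample size. Inputs from the Sample size section: difference 10, SD 16.9, alpha 0.05 (two-sided assumed), power 80%, 1:1 allocation. The standardised effect is 10/16.9 = 0.59. The two-sample t-test needs 45.8, so 46 per arm and 92 in total, with power 0.802. This reproduces. It concerns VISA-A only and is used below just for the denominators.

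**Inputs the documents do not give.** There are no response or missingness rates for the PGIC. All rates below are assumptions.

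**1. Bias when missingness is related to outcome.** Let p be true success in an arm, m the proportion missing, and q success among the missing. Available-case success = (p − m·q)/(1 − m). Take p = 50% in both arms, with m = 20% in the exercise arm and 5% in the heel lift arm.

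- q = 20% (the missing did worse): exercise (0.50 − 0.20×0.20)/0.80 = 57.5%; heel lift (0.50 − 0.05×0.20)/0.95 = 51.6%. The difference is +5.9 points (NNT 1/0.059, about 17) when the truth is zero.
- q = 80% (the missing did better): exercise (0.50 − 0.20×0.80)/0.80 = 42.5%; heel lift (0.50 − 0.05×0.80)/0.95 = 48.4%. The difference is −5.9 points.
- q = 50%: both arms give 50%, with no bias.
- q = 20% with 20% missing in both arms: both arms read 57.5%. Each rate is 7.5 points too high, but the difference stays at zero.

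**2. What the remedies do in the q = 20% case.** Imputing from group alone returns 57.5% and 51.6% in expectation, so the 5.9-point error remains. Counting missing as not effective gives 0.80×57.5% = 46% and 0.95×51.6% = 49%, an error of 3 points in the other direction. The two analyses bracket the truth in this example, but neither is unbiased.

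**3. How much the missing responses could matter with 46 per arm.** Assumed observed response is about 60% against 40%. The last column gives the extreme cases for the missing participants.

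| Missing | Available-case | RD (NNT) | Missing as not effective, RD (NNT) | RD range over all randomised |
|---|---|---|---|---|
| 10% each arm | 25/41 v 16/41 | 0.220 (4.6) | 0.196 (5.1) | 0.087 to 0.304 |
| 20% each arm | 22/37 v 15/37 | 0.189 (5.3) | 0.152 (6.6) | −0.043 to 0.348 |
| 5% v 20% | 26/44 v 15/37 | 0.186 (5.4) | 0.239 (4.2) | 0.043 to 0.283 |

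For the second row, 9 are missing per arm. The lower limit is 22/46 − (15+9)/46 = −2/46 = −0.043, and the upper is (22+9)/46 − 15/46 = 16/46 = 0.348. The analysed total falls from 92 to 82 at 10% missing and to 74 at 20%.

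**The case against.** The strongest reply is that the exemption is declared openly as an exception to a general rule. A reader might infer that the protocol contradicts itself or abandons intention to treat for the PGIC. The text does not support that: intention to treat in its core sense, analysis as allocated, is compatible with missing responses. Nor does the absence of a dropout allowance in the Sample size section conflict with the exemption, because that calculation rests on VISA-A, which is imputed. What stands against the plan is narrower. It states its principle for all randomised participants and departs from it for one efficacy outcome without a reason.

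Two other strong readings also fail. A reader might take the PGIC analysis to be limited to people who completed treatment. It is not, because someone who stopped treatment but answered at week 12 is included. A reader might also conclude that success rates will be overstated. That needs the missing participants to have done worse, but recovered participants may also fail to return, which reverses the sign.

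It is also fair to say that the illustrated bias comes from assumed informative loss, not from the exemption alone, and that the same mechanism would affect the imputed VISA-A and pain VAS. Simply lifting the exemption would change little, since the stated predictors are sex, age, baseline scores and group, and a change rating has no baseline value. This stands, and it shapes the fix. Under Outcome measures, secondary outcomes are collected at 2 and 6 weeks unless stated otherwise, so earlier PGIC and pain VAS should be available to inform the imputation.

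**Conclusion.** The point holds as a departure from the plan's own all-randomised principle for one secondary efficacy outcome. The PGIC comparisons at week 12 will rest on participants with a response, analysed as allocated, while other efficacy outcomes are imputed for everyone. Bias can go either way. It depends on missingness being related to outcome and differing by arm, neither of which the documents quantify. Under the assumed 20% against 5% loss, the spurious difference is 5.9 points in either direction. With 20% missing in each arm, an observed risk difference of 0.189 does not even fix the sign over all randomised participants at the extremes. With little loss over 12 weeks the effect would be small. The primary VISA-A analysis is unaffected. The change is worth making because it is cheap and concerns the measure that yields the NNT.

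**What to change.** - Take self-reported symptom change off the list of variables exempt from imputation. Leave adherence, co-interventions and adverse events unimputed.
- Impute the 7-point PGIC pain and function responses using group, sex, age and baseline scores, and add the week 2 and week 6 PGIC and pain VAS. Confirm against the data-collection schedule that the PGIC was collected at both visits.
- Dichotomise after imputation, pool the relative risk and risk difference, and derive the NNT from the pooled risk difference.
- Add a sensitivity analysis that counts a missing week-12 response as not effective.
- Report the available-case result as well, with the number analysed in each arm.

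The cost is a change of wording and some extra analysis, with no new data collection. The imputed result relies on data being missing at random, which the plan already assumes for VISA-A. The sensitivity analysis shows how far the PGIC result depends on that assumption.

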## Discussion

Achilles tendinopathy is a common musculoskeletal condition causing pain and disability in both sporting and non-active populations. With the increasing number of older and overweight people in the population, the burden of the condition is likely to grow. Eccentric calf muscle loading programs have been the most widely researched and recommended intervention for the management of Achilles tendinopathy [24]. However, this intervention is not without its limitations, the program is demanding and adherence can be challenging [25, 28]. The program has also been found to be less effective in non-active populations, and where the condition is chronic and severe [20, 28]. Therefore, there is a need to evaluate other potentially effective interventions. One such intervention that has been advocated for the management of Achilles tendinopathy is heel lifts. Although evidence exists that shows heel lifts reduce Achilles tendon strain [32] and reduce ankle joint dorsiflexion [31], which suggests that this intervention may be therapeutically beneficial for Achilles tendinopathy, only two low quality studies [29, 36] have evaluated their efficacy for this condition.

Our parallel-group superiority trial with two active treatment groups will be the first randomised trial to compare the efficacy of heel lifts to a calf muscle eccentric exercise program in the management of Achilles tendinopathy. Although we considered including a non-active intervention arm (such as a wait-and-see group) in our protocol, we decided against this as it would not be ethical to withhold treatment as there is already a known effective treatment in the form of a calf muscle eccentric exercise program [73]. We have included a widely used outcome measure as the primary outcome (VISA–A) to allow us to compare the results across other studies that have investigated interventions for Achilles tendinopathy. We have also included a number of secondary outcomes to allow us to capture the effects of interventions on a wide variety of clinically relevant measures. This includes structural integrity of the Achilles tendon, the global rating of change in pain and function, physical activity levels and calf muscle function.

Recruitment commenced in August 2017, and we expect that the results will be finalised by September 2019. Results from this trial will provide clinically relevant information that will assist clinicians in the management of mid-portion Achilles tendinopathy.

## Abbreviations

BMI: Body mass index
CONSORT: Consolidated Standards of Reporting Trials
FPI: Foot Posture Index
MSKUS: Musculoskeletal ultrasound
NHMRC: National Health and Medical Research Council
PGIC: Patient Global Impression of Change
UTC: Ultrasound tissue characterisation
VAS: Visual Analogue Scale
VISA–A: Victorian Institute of Sport Assessment-Achilles
